### Sample size calculation

2.9

The null hypothesis of this study is that there will be no difference in the outcomes between the experimental and control groups when treating chronic neck pain. The hypothesis will be tested using analysis of covariance (ANCOVA) as the primary analytical test. The significance level will be set to α = 0.05 (2-tailed), with type 2 error (β) of 0.2 and a power of 80%. The sample required size was calculated based on a meta-analysis that had analyzed the effectiveness of pharmacopuncture compared to acupuncture or electropuncture therapy in patients with cervical spondylosis.^[12]^ Although the control group of this study differs from ours, we determined that we can utilize that study for sample size calculation based on their findings that the effectiveness of acupuncture in treating neck pain is equivalent^[21]^ or superior^[21,22]^ to that of PT. The mean difference in VAS between the pharmacopuncture and control groups based on this meta-analysis was 1.79 ± 2.74.^[12]^ When effect size is calculated based on this, the f-value is 0.33. Using the G∗Power software, version 3.1.9.4 (Franz Faul, Christian-Albrechts-Universität Kiel, Kiel, Germany), a total of 77 participants will be required. Assuming a withdrawal rate of 20%, we plan to recruit 100 participants.

### Recruitment

2.10

Study participants will be recruited through online media releases, subway advertisements, and promotional posters posted inside and outside the study sites.

### Randomization and allocation concealment

2.11

A statistical expert will randomize an equal number of patients (n = 50, each) into 2 groups, using a random table generated by the nQuery Advisor (Statistical Solutions Ltd., Cork, Ireland) 7.0 (or SAS 9.0 (SAS institute, Cary, USA) or SPSS 21.0 (SPSS Inc., Chicago, USA)) software. The randomization results will be delivered to each institution in sealed opaque envelopes to be stored in a double-locked cabinet. The investigator will provide an adequate explanation of the trial, and each patient that meet the inclusion and exclusion criteria and voluntarily sign the consent form will open a randomization envelope to be randomly assigned a subject number. The investigator will record the assigned random number for each patient on the patient's electronic chart.

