### Study design and setting

2.1

This study is a 2-armed, parallel, multi-center RCT that will be performed on 100 patients in the following institutions: Jaseng Hospital of Korean Medicine, Daejeon Jaseng Hospital of Korean Medicine, Bucheon Jaseng Hospital of Korean Medicine, and Haeundae Jaseng Hospital of Korean Medicine. Participants will be enrolled via competitive recruitment. The study protocol was approved by the institutional review board (IRB) at each institution before starting the participant recruitment process (JASENG 2019-06-009, JASENG 2019-06-010, JASENG 2019-06-011, and JASENG 2019-06-008). Further, the protocol has been registered with Clinicaltrials.gov (NCT04035018) and Clinical Research Information Service (KCT0004243) for continuous updates on the study progress. Information about the healthcare institutions and investigators can be found on the trial registration website.

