#### Experimental group: pharmacopuncture

2.4.1

Pharmacopuncture therapy will be performed twice weekly for 4 weeks. One additional or fewer session per week would be allowed, depending on the patient's status. In other words, a minimum of 1 session and a maximum of 3 sessions can be performed each week. Three sessions per week might be needed in the earlier stages, during which the patient's symptoms might be severe. One session per week might suffice once symptoms have improved. The total number of sessions will not be set in advance. Rather, the physician in charge can make the clinical decisions depending on the patient's status. All procedure-related matters will be recorded in the medical chart for accurate assessment, following the methodology of a study that has analyzed the current use of pharmacopuncture therapy based on the electronic medical records in 12 Korean medicine hospitals.^[9]^ All pharmacopuncture therapies used will be retrospectively reviewed and recorded in the case report form (CRF) for analysis.

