### Statistical methods

2.14

Sociodemographic characteristics and treatment expectancy will be evaluated for each group. Continuous variables will be expressed as mean (standard deviation) or median (quartiles). Differences between the 2 groups will be analyzed using the Student *t* test. Categorical variables will be expressed as frequency (%) and will be analyzed using the Chi-squared test or Fisher exact test.

The endpoint of this clinical trial is the differences in changes in the continuous outcomes (NRS, VAS, NDI, NPQ, EQ-5D-5L, SF-12) at each time point compared to the baseline between the 2 groups. As the primary analysis, ANCOVA will be performed with factors that significantly differ between the 2 groups at baseline as covariates and the groups as fixed factors. As an additional analysis, a linear mixed model will be used to analyze the differences in the changes between visits and the trend of such changes. The linear mixed model will be processed with the mixed model for repeated measures. In addition, the areas under the curve (AUC) will be calculated at each time point after randomization for each outcome during the treatment period and through the entire study period. The Student *t* test will be used to compare the difference in AUC between 2 groups. Additionally, percentages of patients whose NRS and VAS for neck pain decreased by more than 50% from the baseline will be compared for each time point. The time since randomization to the improvement of neck pain, as determined by a drop in the pain indices by more than 50%, will be estimated using the Kaplan–Meier survival analysis. The curves will be compared using the log-rank test. Furthermore, hazard ratios will be compared using the Cox proportional hazard model.

In this study, we will perform both intention-to-treat (ITT) and per-protocol analyses, with ITT analysis as the primary approach. For PP analysis, participants who underwent 6 or more treatment sessions during the 4-week treatment period will be analyzed separately. Missing data in the principal ANCOVA analysis and the AUC analysis will be processed by multiple imputation. Missing time point data in the survival analysis will be censored. All statistical analyses will be performed using the SAS version 9.4 statistical package (SAS Institute, Cary, USA), and differences will be considered statistically significant when *P* < .05.

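### Hospital enters the primary ANCOVA only if it happens to differ significantly between arms, and the article does not say whether randomisation lists are per hospital; the cost is modest precision and a data-dependent adjustment, not bias

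*Protocol article*

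**What the plan says.** - **Setting** (Study design and setting): four hospitals and 100 patients. "Participants will be enrolled via competitive recruitment", so no hospital quota is given.
- **Allocation** (Randomization and allocation concealment): "A statistical expert will randomize an equal number of patients (n = 50, each) into 2 groups, using a random table". The results then go to each institution in sealed opaque envelopes. The section mentions no strata, blocks or hospital-specific lists, rules none out, and does not describe how the table is divided among hospitals.
- **Primary model** (Statistical methods): "ANCOVA will be performed with factors that significantly differ between the 2 groups at baseline as covariates and the groups as fixed factors". Group is the only named fixed factor. Hospital is not named for the ANCOVA, the mixed model, the log-rank test or the Cox model.
- **Treatment delivery** (Experimental group: pharmacopuncture): "the physician in charge can make the clinical decisions depending on the patient's status". The physical therapy arm is equally flexible.

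**The concern.** In a multicentre trial, hospital is a natural factor to balance in the allocation and to carry in the model. Here treatment content is left to the physicians on site, so some difference in outcome between hospitals is plausible, although the article does not document any.

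The analysis section is not simply silent. It states a rule for covariates, and under that rule whether hospital is adjusted for depends on a baseline significance test. There are two possibilities:

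1. **Lists not per hospital.** The arms can be uneven within hospitals by chance, and the rule would nearly always leave that unadjusted.
2. **Lists per hospital.** Balance is secured by design, but a model without hospital keeps between-hospital variance in the error term, so the reported standard error is larger than the true one.

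At stake are some precision and the prespecification of the primary model in a trial where physicians and participants are not blinded.

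**Working it through.** **Inputs from the article.** "The significance level will be set to α = 0.05 (2-tailed), with type 2 error (β) of 0.2 and a power of 80"%; "The mean difference in VAS between the pharmacopuncture and control groups based on this meta-analysis was 1.79 ± 2.74"; "the f-value is 0.33"; "a total of 77 participants will be required"; 20% withdrawal; 100 recruited, 50 per arm; four hospitals.

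**Assumptions, not in the article.** Hospital sizes 25/25/25/25, or 40/30/20/10. Share of outcome variance between hospitals (ICC) 0, 0.02, 0.05 or 0.10. All 100 patients analysed.

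**Step 1: the plan's own figure.** d = 1.79/2.74 = 0.653 and f = d/2 = 0.327. The noncentral F calculation for two groups (λ = f²N) gives N = 76 at f = 0.327, 75 at f = 0.33 and 77 at f = 0.325. The stated 77 is therefore reproduced to within two patients. 77/0.8 = 96.25, so 97, and 100 is a fair rounding. The point below does not change the sample size.

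**Step 2: chance imbalance if there is a single 50:50 list.** With 25 patients per hospital, the number in one arm is hypergeometric (100, 50, 25).
- A given hospital splits 16:9 or worse with probability 0.17.
- By simulation, at least one of the four hospitals has arms differing by 7 or more in about 46% of trials, and by 9 or more in about 21%.
- With sizes 40/30/20/10, the most uneven hospital is 60:40 or worse in about 89% of trials and 65:35 or worse in about 48%.

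**Step 3: would the covariate rule catch it?** A hospital-by-arm chi-squared test (3 df) reaches P < .05 in about 5% of trials, as it must under valid randomisation. Even among equal-size trials where some hospital differs by 7 or more, it does so in only about 12%.

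**Step 4: how far can this move the estimate?** With four hospitals of 25, the variance of the number in one arm at one hospital is 25 × 0.25 × 75/99 = 4.735. The arm difference there has variance 4 × 4.735 = 18.94. The chance hospital contribution to the treatment difference has variance 4 × 18.94/50² × τ² = 0.0303τ², with τ² = ICC × 2.74². Its SD is 0.07, 0.11 and 0.15 VAS points at ICC 0.02, 0.05 and 0.10, against the assumed 1.79. It averages zero.

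**Step 5: effect on the standard error.** Across 100 patients in four equal hospitals, the variance seen by a model without hospital is (1 − ICC) + ICC × 75/99. With hospital in the model it is 1 − ICC.
- Per-hospital blocked lists plus the hospital term: SE ratio r = √[(1 − ICC)/((1 − ICC) + ICC × 75/99)].
- Hospital term on an unstratified list: r × √[1/(1 − 3/99)] = r × 1.0155. The second factor is the price of chance correlation between arm and the three hospital indicators.

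| ICC | Per-hospital lists + term | Term alone, unstratified list |
|---|---|---|
| 0 | 1.000 | 1.016 |
| 0.02 | 0.992 | 1.008 |
| 0.05 | 0.981 | 0.996 |
| 0.10 | 0.960 | 0.975 |

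Simulation of the unstratified case agrees with the last column to within about 0.001.

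**Step 6: error rates.** With an unstratified list, type I error is about 5% with or without the hospital term. With per-hospital lists and no hospital term the test is slightly conservative: from r, about 4.2% at ICC 0.10. Power at N = 100 without either measure is about 0.90. With both it is 0.90 to 0.93 over ICC 0 to 0.10 (equal hospitals).

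**The case against.** The strongest reply has four parts.

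1. **A single list is not stated.** A reader might infer one table running across all four hospitals. Envelopes delivered to each institution fit per-hospital lists just as well, and a condensed article may leave strata and blocks to the full protocol. This stands: nothing here establishes a single list, and the figures in step 2 apply only if there is one.
2. **Chance imbalance is not confounding bias.** A reader might infer from the patient counts that treatment is confounded with hospital. Under valid randomisation that variation is already reflected in the standard error; type I error is not inflated, and the typical displacement is at most about 0.15 VAS points over the range examined. This stands too.
3. **The hospital term is not free.** A reader might expect it to recover the full loss by itself. On an unstratified list it slightly worsens precision at ICC 0 to 0.02 and gains about 2.5% only at ICC 0.10. This also stands.
4. **Hospital variation is not documented.** The hospitals share a standard operating procedure, and physicians decide according to the patient. Differences in delivered treatment might show up as treatment-by-hospital heterogeneity, which a main effect does not remove. This is fair, and it is why the ICC range starts at zero.

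One could add that model terms are commonly left to an analysis plan. That does not dispose of the point, because the article fixes a covariate rule and the rule makes adjustment for hospital depend on a test. Choosing covariates by baseline tests is a wider weakness that also affects baseline VAS; only its consequence for hospital is taken up here.

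**Conclusion.** The point holds in a limited form. The article gives only an overall 50:50 target for four competitively recruiting hospitals and leaves open whether the lists are per hospital. Its covariate rule would admit hospital in about 5% of trials, and only if hospital is counted among the baseline factors tested. Either chance imbalance by hospital is then left unadjusted, or a balanced design is analysed with too large a standard error.

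The cost is 0 to about 4% of the standard error for ICC 0 to 0.10, together with a data-dependent choice in the primary model. The 4% is the gain from per-hospital lists and the hospital term together. The range rests on assumed ICCs and equal hospital sizes. The article does not support a claim of bias, an invalid test or a wrong sample size. The change is worth making because it is cheap and removes a discretionary step, not because the result would otherwise be unsafe.

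**What to change.** - **Analysis.** Prespecify hospital as a fixed factor in the primary ANCOVA and in the mixed model, and as a stratum in the log-rank and Cox analyses, whatever the baseline tests show. Fix this before outcomes are analysed by arm.
- **Randomisation.** State whether the lists are per hospital. For envelopes not yet issued, use concealed permuted-block lists per hospital with varying block size. If the envelopes are already out, make only the analysis change.
- **Cost.** A sentence or two of analysis wording, 3 degrees of freedom, and new lists where still possible. The 77 evaluable and 100 recruited patients stay as they are. If the list is already unstratified and hospital effects are negligible, the standard error rises by about 1 to 1.5%, which is a reasonable price for a model fixed in advance.

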### Blinding

2.12

As it is impossible to blind the physicians delivering the intervention and participants receiving the intervention due to the nature of the interventions, we will only blind the assessors. The resident Essessors, blinded to the participants’ allocation and not involved in the intervention, will perform the evaluations of each outcomes in a separate place, prior to the interventions.

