### Data collection and management

2.13

We will keep in touch with the participants from recruitment to 3 months after treatment to promote participant retention and complete follow-up. The patients will be able to contact researchers at any time to get information they need.

This study will utilize electronic CRF (e-CRF) using the internet-based Clinical Research and Trial management system, managed by the Korea Centers for Disease Control and Prevention. The standard operating procedure (SOP) will be distributed for reference to the study-related procedures, including writing the CRF, entering data, and educating the evaluator and investigators at each site. A data query will be issued for range checking of the data values. Data entered in the e-CRF will be cleaned, locked, and concealed from all investigators, except for the investigator in charge of data management.

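### Section 2.11 issues the subject number by opening an envelope held at the recruiting hospital, so no trial identifier is tied to an envelope before the allocation is visible

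*Protocol article*

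**What the plan says.** Section 2.11 (Randomization and allocation concealment) gives the procedure in four steps.

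1. The list: "A statistical expert will randomize an equal number of patients (n = 50, each) into 2 groups".
2. Custody: "The randomization results will be delivered to each institution in sealed opaque envelopes to be stored in a double-locked cabinet".
3. Assignment: patients who meet the criteria and "voluntarily sign the consent form will open a randomization envelope to be randomly assigned a subject number".
4. Record: "The investigator will record the assigned random number for each patient on the patient's electronic chart".

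Other sections bear on it:

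- Section 2.1 (Study design and setting) names four hospitals and adds: "Participants will be enrolled via competitive recruitment".
- Section 2.2 places consent and screening at the first visit and randomization at the second.
- Section 2.12 (Blinding) says "it is impossible to blind the physicians delivering the intervention and participants receiving the intervention", and that "we will only blind the assessors". Under section 2.7.1 the patient marks the primary VAS.
- Section 2.13: "This study will utilize electronic CRF (e-CRF) using the internet-based Clinical Research and Trial management system".
- Sections 2.15 and 2.18 plan four routine monitoring visits, one close-out visit and one independent audit per site. The monitoring compares CRF with source documents and reviews safety data.

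**The concern.** The weak point is the order of events. The trial identifier is produced by the same act that reveals the arm. Until then, no trial number marks a given patient as the owner of a given envelope, and the stock is in the hospital that recruits. If an opened envelope were set aside, or a patient dropped once the arm was known, the steps described would not by themselves show it.

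At stake is comparability at entry. Blinded assessors do not protect it. Intention-to-treat analysis keeps patients in the arm they were given but cannot undo selection in how they got there. The ANCOVA in section 2.14 adjusts only for factors that differ significantly at baseline, so a modest prognostic imbalance, or one in something not measured, would stay in the estimate.

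A second, smaller matter is that the number of patients per site is unknown when envelopes are sent, which does not sit easily with a promise of exactly 50 per arm.

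**Working it through.** **Inputs from the protocol.** VAS difference 1.79 and SD 2.74, f = 0.33, total 77, 20% withdrawal, 100 recruited (section 2.9); 50 per arm (2.11); four sites (2.1).

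**The plan's own figures.** 1.79 / 2.74 = 0.653, and half of that is 0.327, which rounds to 0.33. A noncentral F calculation gives N = 75 for f = 0.33 and 76 for the unrounded f, close to the stated 77. 77 / 0.80 = 96.25, so 97, which 100 covers. The sample size is not in question here. 100 × 0.80 / 2 = 40 evaluable per arm is used below.

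**1. Would the stated safeguards show a misused envelope?**

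- Seals, opacity and a double lock stop casual viewing. The article does not put the stock under someone independent of recruitment.
- Consent and screening at visit 1 leave a record of the patient, but do not bind that patient to an envelope at visit 2.
- Charting follows opening.
- Monitoring and audit could detect a mismatch between envelopes and charts, but an envelope count is not among the tasks described.

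**2. Can the next allocation be guessed?** The strategy is always to guess the arm assigned less often so far. For a list of n forced to balance, the expected number of correct guesses is n/2 + (2^n / C(n, n/2) − 1) / 2.

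- n = 100, every allocation seen: 50 + 5.8 = 55.8, or 56%.
- A site seeing only its 25 envelopes of one list of 100 (simulation): 51.4%.
- Separately balanced site lists of 24, 24, 26 and 26 (assumed, not stated): 2 × 14.60 + 2 × 15.73 = 60.7 of 100.
- Random blocks of 4, 6 and 8 on separate site lists (assumed): about 67%. Small blocks per site would make guessing easier.

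**3. What would steering do?** Assumptions: a share s of patients is allocated by prognosis, staff recognise prognosis without error, and the gap between good and poor prognosis is g SDs. The spurious difference is s × g × 2.74. The standard error is 2.74 × √(2/40) = 0.613. Type I error is from the noncentral t with 78 df, two-sided 5%, without covariate adjustment.

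| s | g | Spurious difference (VAS points) | Type I error |
|---|---|---|---|
| 10% | 0.5 | 0.14 | 5.6% |
| 10% | 1 | 0.27 | 7.3% |
| 20% | 1 | 0.55 | 14.3% |

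The middle row is 0.274 / 1.79 = 15% of the planned difference.

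**4. Can pre-sent envelopes deliver 50 per arm?** Assume each site holds 50 envelopes (25 per arm) and the sites recruit 40, 30, 20 and 10. The arm total is the sum of four hypergeometric draws. Exactly 50:50 occurs in about 13% of trials, with a 95% range of 44 to 56. The cost is small: at 44/56 the relative efficiency is 4 × 0.44 × 0.56 = 0.986, a loss of 1.4%.

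**The case against.** Sealed opaque envelopes are a recognised method, and the article describes real safeguards: a list made by a statistical expert, a double-locked cabinet, opening by the patient, a chart entry, eligibility screening before visit 2, monitoring and audit. A reader might infer that allocations can be steered without trace. The documents do not support that. An opaque envelope is known to be unwelcome only once opened, the patient opens it, and a discarded one leaves a count that does not tally. What can be said is narrower: no such count is described.

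A reader might also infer that the forced 50:50 split lets sites predict assignments. For one central list it hardly does, at about 1 percentage point over chance for a site that sees only its own share. Material guessing needs short site lists or small blocks, and neither is stated.

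Envelope numbering, an opening log, key-holding and blocking may stand in the full protocol or the operating procedures, so their absence from the article is not the point. This objection stands, but it does not reach the order of events. A fuller document could add sequential numbers; it could not keep the stated order and also assign the subject number before opening.

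Finally, the steering shares and prognosis gaps are assumed, and the t-test calculation leaves out the planned covariate adjustment. That is right, and the figures should be read accordingly.

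**Conclusion.** The point holds in limited form. The stated procedure creates the trial identifier by opening a site-held envelope and records it afterwards, so adherence to concealment cannot be verified from the steps described. This matters more because physicians and patients are unblinded and the patient marks the primary outcome. Exactly 50 per arm cannot be guaranteed with envelopes sent ahead under competitive recruitment, though the resulting imbalance costs little precision.

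Predictability is a side remark (51% to 56% for one list of 100). The bias figures run from 0.14 to 0.55 VAS points and from 5.6% to 14.3% type I error. They show what steering would do under the stated assumptions, and nothing in the documents suggests that it will happen.

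**What to change.** Reverse the order in section 2.11. The site first enters the subject number, confirmed eligibility and completed baseline VAS; the entry is time-stamped and locked; only then is the allocation released from one central list. Use the web-based trial management system if it can do this, which the article does not say, and otherwise the statistician's office.

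If envelopes stay, number them sequentially, assign the subject number before opening, write it with date and signature on the sealed envelope, and reconcile used and unused envelopes at the monitoring visits already planned.

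Treat 50:50 as a target where needed. Do not introduce small random blocks per site, since they would raise predictability.

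The cost is a protocol amendment and a changed step at each site. Central release also depends on internet access or office-hours contact, and the arms may end a few patients away from 50 each.
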